### Blinding

2.5

Patients and raters will not be informed about treatment allocation, and the researcher providing the treatment will not be involved in any assessment. All efficacy assessments will be conducted by blinded researchers who will not be involved in the treatment process. Patients will be advised not to disclose any details of the treatment process to the raters. To test the effectiveness of blinding, at the end of treatment visit (visit 2), we will ask the raters and the subjects to guess the group allocation and analyze their guesses to verify whether the blinding was successful.

### Intervention

2.6

rTMS will be performed using CYY-IIIB Magnetic Stimulator (Yiruide Company, Ltd, Wuhan, China). Subjects in the active stimulation group will receive 10 consecutive days of iTBS mode three times per day, with at least 1 h of interval between each intervention. The stimulation site for the L-DLPFC will be determined using the 10–20 EEG localization system, with stimulation intensity set at 80% of the resting motor threshold (RMT).

Each session will consist of 20 trains, each lasting 2 seconds with an 8-second inter-train interval. Within each train, 10 clusters will be delivered, each cluster containing 3 pulses. The intra-cluster stimulation frequency will be 50 Hz, and the inter-cluster frequency was 5 Hz. The coil will be flipped 90° to deliver sham stimulation. The sham stimulation will also generate a magnetic field that can be felt by the participant, but the field does not penetrate the skull. We plan to deliver 1800 pulses per day to the L-DLPFC in three sessions (with a minimum of 1 h between stimulations) for a total of 10 min per day for 10 days (**Figure 3**).

**Figure 3 f3:**
[figure not shown]
iTBS intervention mode, Each session consists of 20 trains, each lasting 2 seconds with an 8-second inter-train interval. Within each train, 10 clusters are delivered at 5 Hz, each cluster containing 3 pulses at 50Hz. Each cluster lasts 20ms, and the interval between two clusters is 200ms. Three sessions will be conducted each day, with at least a 1-hour interval between sessions, for a total of 10 days.

### Outcome

2.7

#### Primary outcome

2.7.1

Our primary outcome will be the mean change scores of cognitive function assessed using RBANS from baseline to the end of the treatment period. The RBANS, developed by Randolph in 1998, assesses five cognitive domains through 12 subtests, including Attention (Digit Breadth and Encoding Tests), Verbal (Picture Naming and Semantic Fluency Tests), Visual Breadth (Picture Copying and Line Orientation Tests), Immediate Memory (Vocabulary Acquisition and Story Repetition Tests), and Delayed Memory (Vocabulary Recall, Vocabulary Re-recognition, Story Recall, and Picture Recall Tests). We expect that patients receiving active stimulation will show significant improvements in performance on these tests, scoring higher on the total score of the RBANS than the sham stimulation group.

#### Secondary outcomes

2.7.2

The secondary outcome measures of our study will include the changes in the average score of the negative scale of the PANSS scale, the average change in oxyhemoglobin (oxyHb) and deoxyhemoglobin (deoxyHb) in the cerebral cortex.

We will use PANSS to assess the improvement of patients’ clinical symptoms. PANSS is a standardized tool for assessing the severity of symptoms in patients with schizophrenia. It was first proposed by Kay et al. in 1987 (23) and has been widely used in clinical and research settings and has become the gold standard for assessing psychotic symptoms through semi-structured interviews (24). It contains three factors: positive symptoms, negative symptoms, and general psychopathology, with a total of 30 items, each of which is scored on a 7-point scale from 1 (asymptomatic) to 7 (very severe). The total score ranges from 30 to 210, with higher scores indicating more severe symptoms. Given that cognitive impairment is strongly correlated with negative symptoms in patients with schizophrenia (21, 25), we hypothesize that the decrease in PANSS negative symptom scores will be significantly greater in patients receiving active stimulation than in those receiving sham stimulation.

We will use fNIRS technology to record the changes in hemoglobin concentration in the prefrontal cortex during the semantic Verbal Fluency Task (VFT). The VFT is a neurocognitive task commonly used in fNIRS studies and can be divided into phonological and semantic VFTs. The semantic VFT in this experiment will be divided into four phases, and each phase will consist of a 30s resting period and a 30s task period, with a 70s resting period at the end, for a total of 310s (**Figure 4**). During the resting period, the participants will be asked to repeatedly count ‘1, 2, 3, 4, 5’, and during the task period, they will be asked to say as many words as possible belonging to the categories of ‘four-legged animals…’, ‘fruits…’, ‘household appliances’, and ‘vegetables’, respectively, and the researcher recorded the number of words that were correct without repetition. The researcher will record the number of correct words without repetitions. Before starting the task, the participants will be given a practice session to ensure that they understood the task. A meta-analysis has shown that patients with multiple psychiatric disorders experience hypoactivation (e.g., decreased ΔHbO) in relevant brain regions during the VFT task, which may be associated with impaired cognitive function (26). Therefore, we plan to compare fNIRS responses between the two groups, and we expect greater activation in relevant brain regions in the active stimulation group.

**Figure 4 f4:**

fNIRS procedure. The fNIRS testing utilizes a semantic VFT, which comprises four tasks, each preceded by a 30-second rest period, with a 70-second rest period following the final task.

#### Safety monitoring

2.7.3

We will closely monitor possible serious adverse events (SAEs) during treatment. Although previous studies have shown that iTBS treatment is safe and well tolerated in the treatment of depression (27) and schizophrenia (28), based on previous experience, the most common side effect is mild headache, and the most serious side effect is seizure, which is very rare (incidence is approximately 1 in 10,000). Our hypothesis is that there will be no significant difference in the incidence of SAEs between the two groups of patients. If SAEs occur, patients will stop treatment immediately and be unblinded.

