Based on current evidence, we propose an augmented iTBS stimulation protocol for treatment of L-DLPFC based on cognitive function-related circuits in schizophrenia. We plan to deliver 1,800 pulses—three times the standard 600-pulse burst protocol—in order to provide robust, evidence-based data for evaluating the therapeutic efficacy of high-frequency rTMS on cognitive function. The core objective of this study is to validate the safety and efficacy of our proposed augmented iTBS protocol for the treatment of schizophrenia. With this study, we hope to demonstrate that augmented iTBS protocol can have a positive impact in several key areas, including Positive and Negative Syndrome Scale (PANSS) scores on clinical symptoms, Repeatable Battery for the Assessment of Neuropsychological Status (RBANS) on cognitive functioning, and functional near-infrared spectroscopy (fNIRS) on neuroimaging, while we will monitor serious adverse events (SAE) to assess safety.

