### Participant

2.1

We are preparing a double-blind, sham-controlled research project with two randomized subgroups aimed at investigating the clinical effectiveness of a augmented iTBS protocol for the treatment of schizophrenia. Based on a recent meta-analysis of frontal cortex rTMS for improvement of schizophrenia (21), we assumed an effect size of 0.64. Using this assumption and the baseline values as covariates, we concluded that with a power equal to or greater than 80% (β= 0.20), there was a significant difference between the two groups in terms of improvement in cognitive function (α = 0.05), a sample size of 62 calculated using G*Power, and we expected a dropout rate of 10%. Therefore, we plan to include 70 patients who met the DSM-V diagnostic criteria for schizophrenia. We will assign patients to the active stimulation and sham stimulation groups in a 1:1 ratio, and patients participating in the study will be given sequentially numbered patient codes to which the corresponding treatment modality (active or sham stimulation) will be assigned (**Figure 1**). The subjects for this study will be recruited from the inpatients of Zigong Mental Health Centre, who need to meet all the inclusion criteria and not meet any exclusion criteria.

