### Statistical analysis of data

2.8

The normality of the measures will be assessed using the Shapiro-Wilk test. The Levene test will be used to assess the conformity of the variance of the measures. Two independent samples t-test will be used for measures that met normality. The Mann-Whitney U test will be used for measures that did not meet normality. Categorical variables will be analyzed using the chi-square test. Pearson’s correlation analysis will be used to explore the relationship between cognitive function improvement and changes in neural activity. P-value <0.05 will indicate a statistically significant difference.

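### A non-significant SAE comparison with 35 patients per arm cannot support the stated aim of validating safety

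*Protocol article*

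**What the plan says.** The Introduction of the protocol article states: "The core objective of this study is to validate the safety and efficacy of our proposed augmented iTBS protocol". It names one means of judging safety: "while we will monitor serious adverse events (SAE) to assess safety".

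Section 2.7.3 (Safety monitoring) keeps that scope, "We will closely monitor possible serious adverse events (SAEs) during treatment", and sets the expectation for the comparison: "Our hypothesis is that there will be no significant difference in the incidence of SAEs between the two groups of patients". It gives no acceptable difference, no confidence limit to be met and no test.

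The only rule for categorical data is in section 2.8: "Categorical variables will be analyzed using the chi-square test", with "P-value <0.05 will indicate a statistically significant difference".

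Section 2.1 sets the size ("we plan to include 70 patients") and the allocation ("We will assign patients to the active stimulation and sham stimulation groups in a 1:1 ratio"), so 35 per arm. That number comes from an effect size of 0.64 on cognitive improvement. No sample size or power is given for safety.

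The Discussion describes the safety and efficacy data as preliminary and as support for larger trials.

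**The concern.** A significance test of a difference can give evidence that two rates differ. Without a margin and enough patients, failing to reach significance is not evidence that they are alike. Here the objective speaks of validation, the safety measure is SAEs, and the stated expectation is a non-significant difference. Read together, these set up an inference in which a non-significant p-value would count as support for safety.

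SAEs are expected to be few and the arms are small, so that outcome is likely even if the regimen causes a clinically important number of SAEs. A reader of the eventual report could take a foreseeable null result as confirmation that the regimen is safe.

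**Working it through.** **Inputs from the protocol article.** 70 patients at 1:1, so n = 35 per arm (section 2.1). Chi-square for categorical variables at p<0.05 (section 2.8). The article gives no power or expected SAE rate for the safety comparison, so there is no safety figure to reproduce. Its only event rate is for seizure, about 1 in 10,000 (section 2.7.3).

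**Assumptions.** SAE rates of 2%, 5%, 10% and 20% in the active arm, against 0% in the sham arm. Zero in sham makes a difference easiest to detect. The test is two-sided and uncorrected; the article states neither.

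**Step 1: how many SAEs are needed for significance?** For k events against 0 with 35 per arm, the uncorrected statistic is

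X² = 70 × (35k)² / [35 × 35 × k × (70 − k)] = 70k / (70 − k).

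- k = 3: 210/67 = 3.13, p = 0.077.
- k = 4: 280/66 = 4.24, p = 0.039.

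So at least 4 against 0 is needed.

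**Step 2: how likely is a non-significant result?** With no sham events it is the probability of 3 or fewer active-arm events, P(X ≤ 3), where X is binomial with n = 35 and rate p.

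| Assumed true rate, active vs sham | Expected active-arm SAEs (35 × p) | P(non-significant) | Power |
|---|---|---|---|
| 2% vs 0% | 0.7 | 99.5% | 0.5% |
| 5% vs 0% | 1.75 | 90.4% | 9.6% |
| 10% vs 0% | 3.5 | 53.1% | 46.9% |
| 20% vs 0% | 7.0 | 6.1% | 93.9% |

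With a sham rate of 1% instead, enumerating all outcome tables gives a non-significant result in 99.6% of trials for 2%, 93.1% for 5%, 63.6% for 10% and 14.0% for 20%.

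**Step 3: what would zero events show?** The exact upper limit after 0 of n events is 1 − α^(1/n).

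- One-sided 95%: 1 − 0.05^(1/35) = 8.2%.
- Two-sided 95%: 1 − 0.025^(1/35) = 10.0%.

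**Step 4: the one rate that the article gives.** Taking 1 in 10,000 as a per-patient risk, the chance of seeing any seizure among 35 active patients is 1 − (1 − 0.0001)^35 = 0.35%. The trial cannot examine a risk of that order.

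**The case against.** **The sentence is an expectation, not a decision rule.** The article nowhere says that p>0.05 will be reported as proof of safety, safety is neither the primary nor a listed secondary outcome, and the Discussion calls the safety data preliminary. This stands as a limit on the consequences: the primary result is unaffected, and a false safety claim is a risk rather than a certainty. It does not remove the problem, because the objective and the hypothesis remain as worded and the Discussion's more modest description does not agree with them.

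**The chi-square test for SAEs is inferred.** Section 2.7.3 names no test, and a fallback for sparse tables may be in a document that is not shown. This also stands. The argument does not depend on it, since Fisher's exact test would need at least 6 against 0 events and would reach significance less often.

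Three stronger readings are tempting, and the documents do not support them:

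- *That non-significance is near certain whatever the true risk.* It is not: at 20% against 0% chi-square power is 93.9%. The point is strongest for SAE rates up to about 5%.
- *That chi-square is invalid at these counts.* With 35 per arm and a common rate, the exact type I error of the uncorrected test is 1.4% at 3% and 3.6% at 5%. Small expected counts alone do not show invalidity.
- *That there will be no comparative data on non-serious events.* Section 2.7.3 names mild headache as the commonest side effect while the hypothesis covers only SAEs. But section 2.9 refers to a safety evaluation, section 2.10 covers adverse events leading to withdrawal, and routine recording may be described in the full protocol.

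**Conclusion.** The concern holds in this form: the stated safety hypothesis cannot carry the stated safety objective. With 35 per arm and no margin, a non-significant SAE comparison is the likely result across a range of rates that would matter. Its probability is about 99.5% at 2%, 90% at 5% and still 53% at 10%, each against 0% in sham. Observing no SAEs in the active arm would exclude only rates above about 8% (one-sided) to 10% (two-sided).

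These figures rest on assumed SAE rates, on all 35 patients per arm being evaluable for safety, and on the general chi-square rule applying to SAEs. Fewer evaluable patients would widen the limits. The fault is in the inference and its wording; efficacy is not touched.

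**What to change.** 1. In section 2.7.3, delete the hypothesis of a non-significant SAE difference.
2. In its place, state that safety will be described by the number and percentage of patients with SAEs in each arm (and with any adverse event, where recorded) and the risk difference, all with exact 95% confidence intervals.
3. Add a sentence on what the trial can exclude: 0 SAEs in 35 patients rules out only true rates above about 8% (one-sided 95%) or 10% (two-sided 95%).
4. In the Introduction, reword the objective so that it claims no more than the preliminary safety data described in the Discussion.

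The changes are to wording and reporting. They need no additional patients or visits and do not alter treatment. A change from chi-square to Fisher's test is not part of this fix, because it would make significance harder still to reach. The price is a more modest safety claim.

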### Statistical analysis of data

2.8

The normality of the measures will be assessed using the Shapiro-Wilk test. The Levene test will be used to assess the conformity of the variance of the measures. Two independent samples t-test will be used for measures that met normality. The Mann-Whitney U test will be used for measures that did not meet normality. Categorical variables will be analyzed using the chi-square test. Pearson’s correlation analysis will be used to explore the relationship between cognitive function improvement and changes in neural activity. P-value <0.05 will indicate a statistically significant difference.

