### Randomization

2.4

To ensure the scientific rigor and balance of sample allocation, this study will employ a stratified randomization method to evenly distribute 70 samples into two groups. The aim is to minimize the bias in sample allocation and enhance the reliability and reproducibility of the experimental results. Gender is an important potential confounding factor that may influence the study outcomes. Therefore, the samples will be stratified by gender into two layers: the male stratum and the female stratum. Within each stratum, a random number generator will be used to assign a random number to each sample. The random numbers will be generated following a uniform distribution ranging from 0 to 1. Subsequently, the samples within each stratum will be sorted based on the magnitude of the random numbers. The first 50% of samples within each stratum will be allocated to the active stimulation group, while the remaining 50% will be allocated to the sham stimulation group.

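### The sample size is described as baseline-adjusted and randomisation is stratified by sex, but Section 2.8 fixes an unadjusted two-group test; the analysis and the power statement need to be reconciled

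*Protocol article*

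**What the plan says.** Four places in the protocol article bear on this.

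- **Section 2.1 (Participant).** From a meta-analysis, "we assumed an effect size of 0.64". The calculation is then made "Using this assumption and the baseline values as covariates", with at least 80% power and alpha 0.05, giving "a sample size of 62 calculated using G*Power". Allowing for 10% dropout, 70 are to be enrolled, 1:1. The section does not state whether the test is one- or two-sided, which SD the 0.64 refers to, or what baseline-to-end correlation was assumed.
- **Section 2.4 (Randomization).** Allocation is stratified by sex, because "Gender is an important potential confounding factor that may influence the study outcomes".
- **Section 2.7.1 (Primary outcome).** The primary outcome is the change in RBANS from baseline to the end of treatment.
- **Section 2.8 (Statistical analysis of data).** "Two independent samples t-test will be used for measures that met normality"; measures that fail the normality check go to a Mann-Whitney U test. The only other methods named are the chi-square test and Pearson correlation. No covariate, sex term or adjusted estimate appears.

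**The concern.** The sizing paragraph and the analysis paragraph describe different methods for the same comparison. Section 2.1 invokes baseline covariates, while Section 2.8 names tests that cannot use them. The factor singled out in Section 2.4 as prognostic also disappears from the analysis.

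Two things are at stake. The first is precision. In a randomised trial with one baseline and one follow-up measurement, a change score gives baseline a fixed weight of 1 instead of the weight that the data support. The second is the credibility of the 80% power claim, because a reader cannot tell which test it belongs to. If the choice between the two analyses stays open until the data are seen, it also becomes a post hoc choice.

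**Working it through.** **Inputs.** From the article: d = 0.64, alpha = 0.05, power at least 80%, 62 evaluable (31 per arm), 10% dropout, 70 enrolled. Assumed, because the article does not give it: the correlation r between baseline and end-of-treatment RBANS, shown from 0.3 to 0.8, with equal variances at the two times.

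**1. Reproducing the 62.** For a two-sample t-test with 31 per arm, the noncentrality is d × √(n₁n₂/(n₁+n₂)) = 0.64 × √(961/62) = 0.64 × 3.937 = 2.52, on 60 degrees of freedom.

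- One-sided 0.05, unadjusted: power 80.1%, and 31 per arm is the smallest number that reaches 80%. This gives 62 exactly.
- Two-sided 0.05, unadjusted: power 69.8% at 62 and 75.2% at 70 with no dropout. Reaching 80% needs 40 per arm, 80 in total.
- Two-sided ANCOVA F-test with f = d/2 = 0.32 and one covariate, taking 0.64 as already adjusted: 79 in total.
- Two-sided ANCOVA with 0.64 on the raw-score SD: 62 gives 80% only if r is about 0.47 (R² about 0.22).

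Dropout: 62/0.9 = 68.9, so 69. Enrolling 70 is consistent with this and gives equal arms.

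**2. Cost of not adjusting for baseline.** With common variance σ²:

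- Var(change) = 2σ²(1 − r)
- Var(ANCOVA) = σ²(1 − r²)
- Ratio = 2(1 − r)/[(1 − r)(1 + r)] = 2/(1 + r)

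**3. Two-sided power at 62 evaluable.** The standardised effect is 0.64/√(2(1 − r)) for the change-score t-test and 0.64/√(1 − r²) for ANCOVA if 0.64 is on the raw-score SD. If it is on the change-score SD, the effects are 0.64 and 0.64/√((1 + r)/2). ANCOVA here adjusts for baseline only (59 degrees of freedom).

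| r (assumed) | 2/(1+r) | raw SD: change t-test | raw SD: ANCOVA | change SD: change t-test | change SD: ANCOVA |
|---|---|---|---|---|---|
| 0.3 | 1.54 | 55.4% | 73.8% | 69.8% | 86.7% |
| 0.5 | 1.33 | 69.8% | 81.6% | 69.8% | 81.6% |
| 0.6 | 1.25 | 79.2% | 87.2% | 69.8% | 79.1% |
| 0.7 | 1.18 | 89.3% | 93.5% | 69.8% | 76.7% |
| 0.8 | 1.11 | 97.5% | 98.5% | 69.8% | 74.3% |

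ANCOVA has the higher power in every row, but the gain ranges from 18 points to 1 point. On the change-score SD, ANCOVA falls below 80% once r exceeds about 0.57.

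**4. Sex.** The article gives no association between sex and RBANS change, so the gain from a sex term cannot be computed. Its direction is known: leaving out a prognostic stratification factor does not bias the estimate, and it tends to make the standard error slightly too large.

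**The case against.** **The sample size may not rest on an ANCOVA at all.** A reader might infer that the trial was sized on an adjusted analysis and that Section 2.8 throws away precision already counted. The figures do not support that. The 62 is exactly a one-sided unadjusted t-test, and the ANCOVA routes give 79 or need a correlation that the article never states. The covariate may exist only in the wording. This stands, so the point is an unreconciled statement and not a demonstrated loss of planned precision.

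**Baseline is not ignored.** The outcome is a change score, so baseline is subtracted and only the remaining gain, the factor 2/(1+r), is lost. This stands too. The gain shrinks as r rises, and ANCOVA spends a degree of freedom, so a claim that the loss is always material would be too strong. On the raw-score SD at r = 0.7, the t-test alone has 89.3% power.

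**The planned test is valid.** Under randomisation the change-score comparison is unbiased and its type I error is controlled. Omitting sex errs on the conservative side. Nothing in the article supports reading this as bias.

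**A fuller analysis plan may exist, and Section 2.8 speaks only of measures in general.** This does not remove the point. Section 2.8 is not silent: it names the tests for continuous measures, and no exception is made for RBANS. A plan using ANCOVA would contradict the published text, so Sections 2.1 and 2.8 need reconciling either way.

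**Conclusion.** The mismatch is real and stands in the text. It is an efficiency and reporting problem, not a validity problem, and it should be fixed.

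Its size depends on quantities that the article does not give. The change-score variance is larger than the ANCOVA variance by about 1.33 at r = 0.5 and 1.11 at r = 0.8, assuming equal variances at both times. If 0.64 is on the change-score SD, the stated test used two-sided has 69.8% power at 62, about 10 points below the claim; the 80% holds only one-sided. If 0.64 is on the raw-score SD and r is 0.7 or more, the stated test already exceeds 80%. The effect of omitting sex is probably small and cannot be quantified from the article.

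A reader might also infer that switching to ANCOVA restores the claimed power. It need not: on the change-score SD it gives 79.1%, 76.7% and 74.3% at r = 0.6, 0.7 and 0.8. Section 2.1 therefore has to be corrected together with Section 2.8.

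**What to change.** **Section 2.8.** State that the primary analysis is an ANCOVA of end-of-treatment RBANS total score on treatment arm, baseline RBANS total score and sex, reporting the adjusted mean difference with its 95% confidence interval and p-value. Keep the unadjusted comparison of change scores as a sensitivity analysis. Use the same form for the PANSS negative score and the fNIRS outcomes, each with its own baseline.

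**Section 2.1.** State whether the test is one- or two-sided, which SD the 0.64 refers to, and the assumed baseline-to-end correlation. Then restate the power that 62 evaluable patients give under that model. Two-sided, with no credit for the covariate, it is about 70%.

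**Cost.** One or two sentences in each section, one or two degrees of freedom, and possibly a less favourable stated power. No new data are needed, since baseline RBANS and sex are already collected. The change should be dated and made before unblinding.

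### A normality test on the outcome data decides whether the RBANS primary compares mean change or ranks, and neither branch carries the baseline covariate used for the sample size

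*Protocol article*

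**What the plan says.** Section 2.7.1 (Primary outcome) fixes the quantity to be compared: "Our primary outcome will be the mean change scores of cognitive function assessed using RBANS from baseline to the end of the treatment period".

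Section 2.8 (Statistical analysis of data) gives the only between-group rule for continuous measures. It starts with "The normality of the measures will be assessed using the Shapiro-Wilk test". Then "Two independent samples t-test will be used for measures that met normality", and otherwise "The Mann-Whitney U test will be used for measures that did not meet normality". Levene's test is also listed, but nothing follows from its result. The section closes with "P-value <0.05 will indicate a statistically significant difference". It names no separate analysis for the primary outcome. It does not say whether the Shapiro-Wilk test is run per arm, on pooled values or on residuals, and gives it no threshold of its own.

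Section 2.1 (Participant) sets out the sample size: "we assumed an effect size of 0.64", followed by "Using this assumption and the baseline values as covariates". With 80% power and alpha 0.05 it arrives at 62 patients, raised to 70 for 10% dropout.

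**The concern.** Three statements about one primary comparison do not fit together.

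- The outcome section promises a comparison of mean change. The Mann-Whitney test addresses the probability that a patient in one arm scores higher than a patient in the other. It speaks to a location shift only if the two distributions have the same shape. On that branch the trial may answer a different question, and which branch applies is known only once the outcome data have been tested.
- The sample size assumes baseline covariates. Neither the two-sample t-test nor Mann-Whitney takes one.
- Because the pretest is made a decision rule for the primary, its unstated unit and threshold leave discretion over which p-value counts.

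At stake is what a significant or non-significant RBANS result would mean, and whether the analysis matches the basis on which 62 patients were judged enough.

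**Working it through.** **1. The plan's own figure.** Inputs from section 2.1: d = 0.64, alpha 0.05, power 80%, allocation 1:1. Normal approximation per arm: n = 2(z_alpha + z_power)² / d².
- One-sided: 2(1.645 + 0.842)² / 0.4096 = 30.2, so 31 per arm and 62 in total. The exact noncentral t gives 30.9, again 31.
- Two-sided: 2(1.960 + 0.842)² / 0.4096 = 38.3, so 39 per arm and 78 in total.
- Dropout: 62 / 0.90 = 68.9, so 69; the plan says 70.

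The figure of 62 is thus reproduced by a one-sided t-test without covariate, or by a two-sided ANCOVA with a baseline correlation of about 0.47. The article states neither sidedness nor correlation. At 31 per arm a two-sided t-test has 69.8% power.

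**2. How often normal data go to the rank branch.** If the pretest is run in each arm at 0.05 (assumed), the expected share is 1 − 0.95² = 9.75%. Simulation gives 9.8-9.9%.

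**3. What the two-stage rule does.** Simulation with 31 per arm, two-sided 0.05, Shapiro-Wilk in each arm at 0.05, about 8,000 runs per row. Sidedness, pretest unit, pretest threshold and all distributions are assumptions. Ranges show repeat runs. The last three columns give the percentage of trials that reject.

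| Scenario | Sent to Mann-Whitney | t-test | Mann-Whitney | Two-stage rule |
|---|---|---|---|---|
| Normal, no difference | 9.8% | 4.7 | 4.7 | 4.9 |
| t4 in both arms, no difference | 57% | 4.6 | 4.5 | 4.7 |
| Lognormal (sigma 0.5) in both arms, no difference | 93% | 4.7 | 4.7 | 4.9 |
| Normal, shift 0.64 SD | 9.8% | 70-71 | 68 | 70 |
| t4 in both arms, shift 0.64 SD | 56% | 72 | 81 | 80 |
| Lognormal (sigma 0.5) in both arms, shift 0.64 SD | 93% | 71 | 84 | 84 |
| Lognormal (sigma 0.7) in both arms, shift 0.64 SD | 99% | 72-74 | 94 | 94 |
| 25% of active arm shifted by 2.56 SD | 23-25% | 49 | 34-35 | 44-45 |
| Equal means, normal against shifted exponential | 97.5% | 5.3 | 8.3 | 8.3 |

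In the responder row the mean shift is 0.25 × 2.56 = 0.64 sham-arm SD. The mixture raises the active-arm variance to 1 + 2.56² × 0.25 × 0.75 = 2.23, so the shift is only 0.64 / √1.61 = 0.50 pooled SD. That is why even the t-test reaches only 49%.

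For the last row, other runs gave up to 8.9%, and the overall range is about 7-9%. With milder skew in one arm the excess is smaller: 5.8% against 5.0%, or 6.3% against 4.9%.

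**4. How often the choice of test changes the result.** At a 0.64 SD shift, the t-test and Mann-Whitney disagree on significance in 6.6% of trials (normal), 12.4% (t4) and 15.0% (lognormal, sigma 0.5).

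**5. What the omitted covariate is worth.** With baseline correlation ρ, the ANCOVA effect is f = 0.32 / √(1 − ρ²). Assume ρ = 0.5. The SD of change, √(2(1 − 0.5)) = 1, then equals the SD of the score, so 0.64 applies on both scales. This gives f = 0.32 / 0.866 = 0.37 and noncentrality 62 × 0.37² ≈ 8.5. Two-sided power with 62 patients is 81-82%, against 70% for the t-test on change.

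**The case against.** The case against has real force, and several stronger readings should not be drawn.

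- **Inflated type I error.** A reader might infer this from the two-step procedure. When both arms share a distribution, the rule rejects in 4.4-5.2% of null trials across all runs. The excess appears only with equal means and unequal shapes, a pattern for which the documents give no evidence.
- **A general loss of power.** A reader might infer that the rank branch costs power just where non-normality is likely. The responder mixture does cost about 5 points, but it reaches the rank branch in only about a quarter of trials. Where both arms are heavy-tailed or skewed, the rule gains 8 to 20 points or more. It cannot be said that switching buys little.
- **Free choice after seeing the data.** The rule is written in advance, and Shapiro-Wilk within arms does not look at the treatment difference. What depends on the data is which branch applies.
- **The covariate gap belongs to Mann-Whitney.** It does not: the t-test branch omits the covariate too. Deleting the pretest alone would leave that gap open.
- **No estimate could be reported.** A rank p-value does not stop a mean difference and interval being shown, and an article may leave reporting detail to the analysis plan.

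With normal data, moreover, sending 10% of trials to the rank test changes power and error hardly at all. What the objection does not remove is the mismatch in the text: the outcome is a mean change, one branch does not test it, and neither branch matches the sample-size model.

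**Conclusion.** The concern holds as a mismatch between outcome, test and sample size. It does not hold as a claim of inflated error or consistent loss of power. As written, an outcome-data pretest with no stated unit or threshold selects the target of the primary test. About 10% of trials with perfectly normal data would take the rank branch, and most trials with clearly skewed data would. If the arms differ in shape but not in mean, about 7-9% of trials would be called positive, against about 5% for the t-test. The power effect runs from a loss of about 5 points to a gain of about 20, depending on distributions the article does not give. These figures rest on 31 per arm, two-sided 0.05 and a per-arm pretest at 0.05, all but the first being assumptions. The mismatch between sections 2.1, 2.7.1 and 2.8 needs no simulation. It should be corrected before unblinding.

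**What to change.** State one primary analysis for RBANS in section 2.8: a linear model (ANCOVA) of the RBANS total score, or its change, on treatment and baseline RBANS. Report the adjusted mean difference with a 95% confidence interval. Use this model whatever the Shapiro-Wilk or Levene result, with robust or bootstrap standard errors if the residuals look poor. Keep Mann-Whitney as a labelled sensitivity analysis, and drop the normality test as a decision rule.

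This takes a few sentences and uses data already planned for collection. The target is then the mean change that section 2.7.1 names, and the model carries the covariate that section 2.1 assumes. The cost is some power relative to a rank test if the data are strongly skewed or heavy-tailed in both arms (in the assumed cases above, about 72% against 80-94% before any gain from the covariate). The article reports recruitment as still under way, so the change can be dated and recorded before unblinding.
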